### Primary outcome

To evaluate the effectiveness of EA treatment over the sham device for poststroke UR, we will primarily assess the change in daily PVR urine ratios between the baseline and end point of the last session. The daily PVR ratio is computed by dividing the daily PVR urine volume by the daily PVR urine volume plus spontaneous voiding volume. The daily PVR urine volume for 24 hours will be examined with ultrasonography scanning. If the PVR urine volume is more than 100 mL, the residual will be removed through intermittent cauterization before the scanning. When spontaneous urination is impossible, a 24-hour weight change in diaper will be measured for the self-voiding volume.

If the urinary tract is infected at the end, the outcome assessor will measure the PVR urine volume on the third day of the last session after anti-UTI treatment for 48 hours. Otherwise, PVR urine volume will be measured on the next day of the last session.

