### Inclusion criteria

We will include both male and female patients aged >19 years whose stroke episodes occurred within the last 2 years. We will not restrict inclusion of participants according to type of stroke or damaged region in the brain. Stroke history will be confirmed based on computed tomography or magnetic resonance imaging examination results. Two consecutive PVR tests will be performed, and the patient with the results of both residuals > 100 mL will be included in the trial [1, 2].

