### Sample size

Based on a previous study [2], the mean percentage change in PVR ratios in the EA and control groups were computed. We assumed an after-treatment PVR ratio of 0.65 in the control group, as it was not reported in the study. The null hypothesis was that the percentage changes in PVR ratios have no significant difference between the intervention and control groups. With a significance level of 0.05 and a statistical power of 0.8, the calculated sample size in total was 42 [28]. Considering a 20 % drop rate at a 1:1 allocation ratio, we will recruit 27 participants for each group.

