Bladder dysfunction, including UR, poses an obstacle for rehabilitation and QoL improvement in poststroke patients [2, 4–6]. Catheterization, the major therapeutic approach, confers the risk of UTI [2]. A preliminary clinical study showed the potential benefits and safety of EA treatment for stroke patients with UR [2]. However, the study was performed only with a single group and lacked the methodological requirements and statistical power to establish the evidence for treatment. Overall, clinical trials of EA for any urinary dysfunction, with a placebo control, are rare, except for the study of poststroke detrusor overactivity [11]. We targeted UR in poststroke patients and designed a randomized, sham-controlled trial to be conducted in multiple sites to appropriately generalize the results of the trial, following the CONSORT [12] and STRICTA guidelines [13].

At the end of the project, we expect that the findings will provide clinical evidence of the effectiveness of EA treatment for improving UR in stroke survivors.

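### The primary-outcome rule places drainage of residuals above 100 mL before the ultrasound scan that measures them, and does not say which volume enters the PVR ratio

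*Protocol article*

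**What the plan says.** All of this is in the Protocol article.

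- **Outcome (Primary outcome):** "we will primarily assess the change in daily PVR urine ratios between the baseline and end point of the last session". The ratio is obtained by "dividing the daily PVR urine volume by the daily PVR urine volume plus spontaneous voiding volume".
- **Instrument (Primary outcome):** "The daily PVR urine volume for 24 hours will be examined with ultrasonography scanning". No other source for the residual volume is named.
- **Drainage (Primary outcome, next sentence):** when the PVR exceeds 100 mL, "the residual will be removed through intermittent cauterization before the scanning".
- **Entry (Inclusion criteria):** two consecutive tests are done, and "the patient with the results of both residuals > 100 mL will be included in the trial".
- **Planning value (Sample size):** "We assumed an after-treatment PVR ratio of 0.65 in the control group".
- **Procedure name:** the drainage sentence says cauterization. The Background and Discussion speak of catheterization, for example "Catheterization, the major therapeutic approach, confers the risk of UTI".

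**The concern.** The volume to be measured is, on the page, removed before the measurement. The scan mentioned in the drainage sentence can only be the ultrasonography named one sentence earlier. The order also cannot be carried out as it stands, because nobody knows that a residual exceeds 100 mL until it has been read. The article does not say that the triggering reading is kept, or that the drained urine is measured and added to the daily PVR.

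At stake is the meaning of the primary outcome. A site that follows the sentence to the letter would record what is left after drainage. A site that scans and then drains would record the true residual. A site that adds catheter volumes would record something else again. All three would be entered under the same variable name, in a trial of three hospitals and 27 patients per arm. If pre-drainage volumes were never written down, no analysis could recover them.

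**Working it through.** **The plan's own sample size.** The total of 42 is 21 per arm. With 20 % dropout, 21/0.8 = 26.25, rounded up to 27 per arm, or 54, so that step reproduces. The 42 itself cannot be checked, because the article gives no standard deviation, baseline ratio or EA-arm ratio. The point here is measurement order, so the relevant planning figure is the control ratio of 0.65.

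**Formula.** Ratio = R/(R + V), with R the residual and V the spontaneously voided volume per scan. It rises with R for any V above zero.

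**Check 1: does the literal order fit 0.65?** If everything above 100 mL is drained first, no scan can show more than 100 mL. The largest recordable ratio is then 100/(100 + V). Setting this to 0.65 gives V = 100 × 0.35/0.65 = 53.8 mL. A ratio of 0.65 is reachable only if about 54 mL or less is voided per scan.

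**Check 2: what happens around 100 mL?** The article gives no volumes. The table assumes V from 50 to 300 mL and 10 mL left after drainage.

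| V (mL) | Largest ratio with 100 mL scanned | R = 90 mL, not drained | R = 101 mL, read before drainage | R = 101 mL, read after drainage |
|---|---|---|---|---|
| 50 | 0.67 | 0.64 | 0.67 | 0.17 |
| 100 | 0.50 | 0.47 | 0.50 | 0.09 |
| 150 | 0.40 | 0.375 | 0.40 | 0.06 |
| 200 | 0.33 | 0.31 | 0.34 | 0.05 |
| 300 | 0.25 | 0.23 | 0.25 | 0.03 |

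For example, at V = 150: 90/240 = 0.375; 101/251 = 0.40; 10/160 = 0.06. In every row the 101 mL patient, read after drainage, scores better than the 90 mL patient. The direction does not depend on V. It needs only that less remains after drainage than in the undrained patient.

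**Check 3: a true ratio of 0.65.** The residual required is R = V × 0.65/0.35, which is 186 mL at V = 100 and 557 mL at V = 300. Both exceed 100 mL and would be drained. Read before drainage, the ratio is 0.65. Read after drainage with 10 mL left, it is 10/110 = 0.09 down to 10/310 = 0.03. With 30 mL left it is 30/130 = 0.23 down to 30/330 = 0.09. With complete emptying it is 0.

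**Who is affected.** Entry requires two residuals above 100 mL, so every participant meets the drainage trigger at screening and nearly all would be expected to meet it at baseline. At the end point it applies to those still in retention.

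**The case against.** The strongest reply is that the sentence does not describe what anyone would do. It opens with a condition on the PVR volume, so a reading must already exist, and nothing says that reading is discarded. The outcome covers 24 hours, so the authors may have meant to empty the bladder before the window opens, to scan and then drain, or to count the catheter volume. The planning ratio of 0.65 points the same way: it is hard to reach under the literal order, which suggests a badly worded sentence more than an intended measurement. The article is also condensed, and scan-by-scan procedure may sit in a fuller document.

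Most of this stands, and it limits the conclusion. A reader might infer that patients in retention will be recorded as nearly empty, that the outcome is non-monotone, and that baseline leaves no room for improvement. The documents do not support these as facts. Each holds only if the sentence is followed to the letter, drainage is nearly complete and drained urine is not counted, and the size rests on assumed volumes.

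The reply does not remove the ambiguity. The alternative readings are different procedures and the article states none of them. Condensation can excuse missing detail, but here an order is stated, and it is circular. The word cauterization is evidently a slip for catheterization. It has no statistical consequence and adds no weight.

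**Conclusion.** The point holds as an ambiguity in the definition of the primary outcome, and it should be corrected. The stated order is circular, and the article does not settle whether the pre-drainage reading, the drained volume or the post-drainage scan enters the ratio. That much needs no assumption.

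The consequences are conditional. On the literal reading, a true ratio of 0.65 would be recorded as about 0.03 to 0.09, assuming 100 to 300 mL voided per scan and 10 mL left, and the ranking of patients could reverse at 100 mL. The conflict with 0.65 needs fewer assumptions: at most 100 mL scanned requires about 54 mL or less voided per scan. On any other reading the distortion may be absent, but between-site differences in what is recorded remain possible. Nothing shows that the authors chose to scan after emptying.

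**What to change.** Rewrite the measurement sentence so that:

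- the PVR entering the ratio is the ultrasound reading taken before any urine is removed, summed over the 24 hours;
- this one source is used at every site and at both baseline and end point, with no option to substitute the drained volume;
- urine later drained is already counted through that reading, so it is neither dropped nor counted a second time in the numerator or denominator.

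Reconcile cauterization with the catheterization named in the Background and Discussion, as a wording correction. When to drain stays with the clinical team.

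The cost is one sentence in the protocol or site manual and a case-report-form field for the pre-drainage reading. No extra procedure should be needed, since the 100 mL trigger already presupposes a reading. The abstract describes recruitment as under way, so each site should also confirm which volume it has recorded for any patient already measured.

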### Secondary outcome

Because UTI might affect the urine residuals [18, 19], the patients in both groups will undergo urinalysis to determine whether UTI exists before PVR urine volume evaluation at the end point. UTI is diagnosed when nitrite is detected by urinalysis and two of the following clinical symptoms exist: pyuria, lower abdominal pain, or hematuria [20]. The urinalysis retest is performed after 48 hours of antibiotics treatment.

We will also assess disease-specific QoL by using the Korean version of the Qualiveen Questionnaire (K-QQ). This is an assessment tool consisting of 30 items for patients with neurogenic bladder [21–24]. Each item, rated from 0 to 4 points, evaluates patients’ bladder problems, while the additive nine questions, rated from −2 to +2 points, are about patients’ general QoL status. The higher the absolute value of the total K-QQ score, the lower the QoL becomes. We will measure the K-QQ scores at baseline and at the end of the last session.

The Korean version of the International Prostate Symptom Score will be assessed at baseline and at the end point. This scale is generally used to evaluate general symptoms related to the lower urinary tract [25, 26]. The total score (0–35) is calculated by seven items of 0–5 points each, and the severity will be assessed as mild (0–7 points), moderate (8–19 points), or severe (20–35 points).

The frequencies of urination and urinary incontinence will also be reported. The patients will record them by urinary diary for 1 day before the first intervention and for another day after the last intervention. The mean change from posttreatment to pretreatment in the EA group will be compared with that in the sham group.

Finally, we will measure the blinding index (BI) for all of the participants at the end of the verum or the sham EA. The success or failure of the participants’ blinding will be assessed by using the validated scale [27]. The outcome assessor will ask the participants where they belong by selecting one of the following responses: “I think I belonged to the EA group,” “I think I belonged to the sham group,” or “I don’t know which group I belonged to.”

The patient-rated outcomes will not be measured when the participants are unconscious. The two caregivers with more than 1 year of practical experience, after being educated about the scales, will independently fill in the scales for the participants with low cognitive function and the discrepancy will be settled through discussion.

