### Data analysis

We will analyze results primarily based on the principle of intention - to - treat (ITT) and subordinately based on the per - protocol (PP) principle. The ITT analysis will include any participants who are randomly allocated and have at least one EA or sham session. Missing values will be imputed by the last observation carried forward. The PP analysis will cover only the patients who have at least seven sessions of EA or sham treatments and have no medical diagnosis of UTI at the end point.

Continuous variables will be tested by the independent *t*-test if normality is obtained. Otherwise, the Mann-Whitney *U* test will be implemented. The categorical variables will be analyzed by the Pearson *χ*^2^ test or Fisher's exact test.

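### The K-QQ absolute-value rule does not order patients consistently if the nine signed general QoL items enter the total

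*Protocol article*

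**What the plan says.** All the scoring information is in the K-QQ paragraph of the Protocol article, section Secondary outcome.

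- Length of the instrument: "This is an assessment tool consisting of 30 items for patients with neurogenic bladder".
- Bladder items: "Each item, rated from 0 to 4 points, evaluates patients’ bladder problems".
- General QoL items: "while the additive nine questions, rated from −2 to +2 points, are about patients’ general QoL status".
- Direction: "The higher the absolute value of the total K-QQ score, the lower the QoL becomes".
- Timing: "We will measure the K-QQ scores at baseline and at the end of the last session".

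The section Data analysis then applies to the K-QQ as to any other continuous outcome: "Continuous variables will be tested by the independent" t-test when normality holds, and by the Mann-Whitney U test when it does not.

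The article does not say whether the nine general questions lie inside the 30 items or come on top of them, or whether +2 is the good or the bad end of those questions. No other section defines the total or its direction.

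**The concern.** The two parts of the questionnaire are built differently. A 0 to 4 bladder item has its best state at zero and gets worse in one direction. A −2 to +2 item has its best state at one end and its worst at the other, with zero in the middle. Taking the absolute value of a sum of the two treats zero as the best result, and zero is the best result only for the bladder part.

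Both planned tests need a score in which higher always means the same thing. If it does not, improvement in one part can offset improvement in the other, or a patient who improves on both parts can be recorded as worse. A real effect on quality of life could then be diluted, or in some patients reversed.

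**Working it through.** The article gives no range, mean or standard deviation for the K-QQ, so there is no figure of its own to reproduce. The check uses only the stated item ranges.

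**Inputs (Protocol article, Secondary outcome).** Let B be the sum of the 0 to 4 bladder items, with higher meaning worse. Let G be the sum of the nine general items, so G runs from 9 × (−2) = −18 to 9 × (+2) = +18. The total is T = B + G, and the rule reads |T| as impairment.

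**Range of T.**
- Nine items on top of 30: B runs from 0 to 30 × 4 = 120, so T runs from −18 to 138.
- Nine items among the 30: B runs from 0 to 21 × 4 = 84, so T runs from −18 to 102.

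T can be negative either way. Whatever the sign of the general items, totals of −18 and +18 receive the same score.

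**If +2 is the better state.** Whenever T > 0, |T| = B + G, so better general QoL raises the impairment score.
- B = 40, G = −18 (worst general QoL): |40 − 18| = 22.
- B = 40, G = +18 (best general QoL): |40 + 18| = 58.
- Change within a patient: from B = 60, G = −18 (score 42) to B = 50, G = 0 (score 50). Both parts improve, and the score worsens by 8.
- Across an arm, while totals stay positive, a fall of x in B and a rise of x in G cancel exactly: −x + x = 0.

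**If +2 is the worse state.** Whenever T ≥ 0, |T| = B + G and the order is right. It fails only when T < 0. Since G cannot go below −18, that requires B < 18.
- B = 0, G = −18 (best possible state): |0 − 18| = 18.
- B = 18, G = −18 (worse bladder, same general QoL): |18 − 18| = 0.
- Change within a patient: from B = 10, G = −10 (score 0) to B = 2, G = −18 (score 16). Both parts improve, and the score worsens by 16.

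**How often.** As an illustration, pairs of patients were drawn from a uniform grid of all (B, G) values. The pairs kept were those where one patient is at least as bad on both parts and strictly worse on one. The share that |T| puts in the wrong order was:

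| Sign of the general items | 30 + 9 items | 21 + 9 items |
|---|---|---|
| +2 is better | about 18% | about 25% |
| +2 is worse | about 0.4% | about 0.9% |

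Real scores will not be uniform, so these shares show only the contrast between the two signs. Negative totals fill 171 of 121 × 37 = 4,477 grid cells (3.8%) with 30 + 9 items, and 171 of 85 × 37 = 3,145 (5.4%) with 21 + 9.

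**After correction.** With the nine items signed so that higher is worse and no absolute value taken, T = B + G rises with worsening in either part, and no reversals remain.

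**The case against.** The strongest defence is that the article never says outright that the nine items are summed with the others. In "while the additive nine questions" the adjective may simply mean additional. If the total is the sum of the 0 to 4 items alone, it cannot be negative, the absolute value changes nothing, and higher always means worse. This reading is possible. Its weakness is that it leaves the absolute value without a purpose: nobody needs one for a score that starts at zero. Applying the absolute value to the nine-item score alone does not help either, because the best and worst general QoL would then score the same.

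A second defence is that the article cites sources for the instrument, and a condensed protocol may leave item signs and subscale scoring to them. That stands: the unstated sign is not a fault in itself. The fault is the direction rule that the article does state, which fails under either sign once the general items are included.

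A reader might go further and infer that the score cannot order patients at all, or that the QoL comparison between arms is uninterpretable. The documents do not support that. If +2 is the worse state, every comparison between non-negative totals is correct, and negative totals need a low bladder sum, perhaps uncommon in patients enrolled for retention. Nor can a single range of −18 to 138 be taken as given, since the nine items may be among the 30.

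**Conclusion.** The concern holds in a limited form. If the signed general items enter the K-QQ total, the stated rule does not order patients consistently, whichever end of the −2 to +2 scale is good. The effect is broad if +2 is better, because general QoL then counts the wrong way for every positive total. It is narrow if +2 is worse, because only comparisons involving a total below zero are affected.

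The conclusion rests on one assumption, that the nine items are part of the total. The wording favours this, since the absolute value otherwise does nothing, but it does not settle it. The conclusion does not depend on the sign of the items or on whether there are 30 + 9 or 21 + 9; those determine only its size.

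The K-QQ is a secondary outcome. The primary PVR-ratio comparison and the sample size are untouched. The rule should be corrected before the data are unblinded, but it does not threaten the trial's main conclusion.

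**What to change.** In Secondary outcome, delete the absolute-value sentence and replace it with a scoring definition that states:

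1. which items form the K-QQ score, and whether the nine general questions are within the 30 or additional to them;
2. which end of the −2 to +2 scale is the better state;
3. one of two ways to report: the bladder-impact score (higher is worse) and the signed general QoL score separately, each with its direction; or a single signed total after both parts are recoded to the same direction.

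Separate reporting is the simpler choice, because it avoids weighting two different constructs against each other. The tests named in Data analysis can stay as they are; this point calls for no change to the statistical model.

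The cost is a few lines of scoring text. The questionnaire, the visits and the data collected do not change.

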### Other outcomes

Information on diabetes mellitus (DM) and benign prostatic hyperplasia (BPH) will be obtained from the participants’ medical history.

### Safety assessment

Adverse events will be reported to evaluate the safety of EA for poststroke patients with UR. The questionnaires will be administered to the participants after every verum or sham EA session, and the results will be recorded and analyzed. The outcome assessors will judge the severity (mild, moderate, or severe), seriousness, and causality (definitely related, probably related, possibly related, possibly not related, definitely not related to the intervention, or not assessable).

### Sample size

Based on a previous study [2], the mean percentage change in PVR ratios in the EA and control groups were computed. We assumed an after-treatment PVR ratio of 0.65 in the control group, as it was not reported in the study. The null hypothesis was that the percentage changes in PVR ratios have no significant difference between the intervention and control groups. With a significance level of 0.05 and a statistical power of 0.8, the calculated sample size in total was 42 [28]. Considering a 20 % drop rate at a 1:1 allocation ratio, we will recruit 27 participants for each group.

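### The null hypothesis, sample size and 80% power are stated for percentage change in PVR ratio, but the primary outcome is change in the ratio, so the power claim is not tied to it

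*Protocol article*

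**What the plan says.** The Primary outcome section of the protocol article says: "we will primarily assess the change in daily PVR urine ratios between the baseline and end point of the last session". It defines the ratio as residual volume divided by residual plus spontaneously voided volume, and does not mention a percentage change.

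The Sample size section works with a different quantity. It says: "Based on a previous study [2], the mean percentage change in PVR ratios in the EA and control groups were computed". It then adds: "We assumed an after-treatment PVR ratio of 0.65 in the control group, as it was not reported in the study". The hypothesis follows on the same scale: "The null hypothesis was that the percentage changes in PVR ratios have no significant difference between the intervention and control groups". The result is: "With a significance level of 0.05 and a statistical power of 0.8, the calculated sample size in total was 42". The last step is: "Considering a 20 % drop rate at a 1:1 allocation ratio, we will recruit 27 participants for each group".

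Of the source study, the Discussion says: "the study was performed only with a single group". The Background describes it in the same way.

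The Data analysis section assigns continuous variables to an independent t-test or, failing normality, a Mann-Whitney test. It does not say on which scale the primary variable is analysed.

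**The concern.** The PVR ratio is already a proportion. Its change is a difference between two proportions. Its percentage change divides that difference by the patient's own baseline, so patients with a low baseline carry much more weight. The two variables have different means, different variances and different standardised effects, and power computed for one does not carry over to the other.

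Two things are at stake. First, the 80% is a statement about a test that the Primary outcome section does not define. Second, the article alone lets an analyst defend either scale, and the two can fall on opposite sides of 0.05.

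A related weakness lies in the planning effect. The changes in both arms are said to rest on one earlier study, yet by the protocol's own account that study had no control arm. The control end value of 0.65 is therefore an assumption with no data from that study behind it.

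**Working it through.** **1. The plan's own figures.** Inputs from the Sample size section: alpha 0.05, power 0.80, 42 evaluable patients (21 per arm), 20% dropout, 1:1 allocation. Sidedness is not stated and is taken as two-sided.

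- Dropout step: 21 / (1 − 0.20) = 26.25, rounded up to 27 per arm, 54 in total. This reproduces.
- Core step: the 42 cannot be reproduced, because the article prints no EA mean, baseline ratio, difference or SD. It can only be inverted. By normal approximation, d = (z₀.₉₇₅ + z₀.₈₀) × √(2/21) = (1.960 + 0.842) × 0.3086 = 0.865. With the noncentral t distribution, d = 0.886. One-sided values would be 0.77 and 0.78.

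So 42 evaluable patients give 80% power for a standardised difference of about 0.89 in an unadjusted two-sided t-test, on whichever scale that difference is expressed.

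**2. The scales can rank patients differently.**

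| Patient | Baseline | End | Change | Percentage change |
|---|---|---|---|---|
| A | 0.80 | 0.60 | −0.20 | −0.20/0.80 = −25% |
| B | 0.30 | 0.15 | −0.15 | −0.15/0.30 = −50% |

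A improves more on the first scale, B on the second.

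**3. Power on the two scales for the same data.** All values are assumed, because the article prints only the 0.65: mean baseline 0.70, end means 0.65 (sham) and 0.45 (EA), residual SD 0.22, ratios kept within 0–1, 21 per arm, two-sided t-test. The effect is either constant or proportional to baseline.

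| Baseline SD | Constant: change | Constant: % change | Proportional: change | Proportional: % change |
|---|---|---|---|---|
| 0.10 | 82% | 81% | 82% | 80% |
| 0.15 | 82% | 79% | 80% | 75% |
| 0.20 | 81% | 75% | 78% | 67% |
| 0.25 | 80% | 72% | 76% | 57% |

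The gap grows with the spread of baseline ratios. In every row, change in ratio has the higher power.

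**4. How often the two tests disagree.** Assumptions: 27 per arm, residual SD 0.20, baseline ratios uniform from 0.2, 0.3 or 0.5 up to 1.0, constant or proportional effect, effect sized for power near 80% on the change scale. The two t-tests fall on opposite sides of p = 0.05 in about 5% of simulated trials with the narrowest baseline range and up to about 21% with the widest.

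**The case against.** The strongest defence is that there is only one primary outcome here, loosely worded. Only one section carries that heading, the other is a planning paragraph, and the Primary outcome section never says absolute change. The full protocol or an unseen analysis plan may settle the scale. Part of this stands: it is an ambiguity to close, not proof that two primary outcomes were declared. But the article does not merely leave the scale out. It prints one quantity for the outcome and another for the hypothesis, and no section describes the outcome as a percentage change.

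A second objection is that the 0.65 is already declared an assumption. That is correct, so there is no concealment. What remains is loose wording: the changes in both arms are said to be based on a study that had only one.

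A reader might infer that the trial is underpowered. The documents do not support this. They give no effect or SD on either scale, and in the simulations the defined outcome has the higher power. A reader might also infer that power collapses if 0.65 is wrong. A different control value could move power either way, and without a printed SD on the planning scale the amount cannot be given.

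Finally, baseline adjustment could be called a third variable. It is a preference, not a correction of an error. However, with baseline as a linear covariate, the end ratio and the change in ratio give the same treatment estimate, so adjustment stays with the defined outcome. The objection is right that the 0.89 belongs to an unadjusted test and must be labelled so.

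**Conclusion.** The point holds as an inconsistency between the primary outcome and the hypothesis that was powered. The outcome is change in the PVR ratio, while the null, the 42 and the 80% refer to percentage change. The stated power is therefore not tied to the defined primary outcome. This rests on the text alone and is firm.

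The size is conditional. Disagreement on significance in about 5–21% of trials depends on the assumed SD of 0.20, 27 per arm and the assumed baseline ranges. The direction and amount of any true power discrepancy cannot be determined from the documents.

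No arithmetic error is shown: the dropout step is right and the 42 cannot be checked. Wording the null as no significant difference describes a test result and not a parameter, but that is minor.

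**What to change.** - Name one primary variable in the Primary outcome, Sample size and Data analysis sections. The preferred choice is the end-of-study PVR ratio compared between arms with adjustment for the baseline ratio, which is already collected. The minimum is to use change in ratio consistently.
- State the null hypothesis as equal means in the two arms on that scale.
- Restate the size claim: 21 evaluable patients per arm give 80% power for a standardised difference of about 0.89 in an unadjusted two-sided t-test at 0.05. If the adjusted analysis is adopted, add that adjustment is expected to keep or raise that power.
- Reword the attribution so that only the EA-arm figures are credited to the earlier study, and keep 0.65 as a declared assumption.

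The cost is wording only. The power claim becomes openly conditional on an assumed effect and looks less firm. Enrolment stays at 54.
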